- Significant improvement in dietary diversity in children in the egg program vs. controls
- No observed changes in breastfeeding practices in children from either group

1. **Eligibility Criteria**
   1. **Inclusion Criteria**

- Healthy children ages 6 to 24 months at the time the study begins
- No cerebral palsy, birth defect or condition that may affect their growth or development.
- Children living in Intibucá, Honduras in Camasca, Concepción, Colomoncagua, Santa Lucía, or San Marcos de Sierra
  1. **Exclusion Criteria**
- Children from families that are considering leaving the region within the next 12 months
- Known egg allergy

1. **Study Design**

This is a prospective, community-cluster study that will evaluate the effectiveness of a program that will provide 30-day egg vouchers to mothers of 6 to 24 month-old children living in rural areas of Intibucá, Honduras. The program will be delivered by a local non-profit organization (Shoulder to Shoulder - Hombro a Hombro). This research study consists of a survey that will be implemented at baseline, 6 months and 12 months. (Jan 2021-Jul 2021-Jan 2022)

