**Endline assessment:**

Dietary, morbidity, anthropometry, food insecurity survey, adherence

Visit 3

Jan 2022

1. **Enrollment**

The AIN- C program is a community-based health promotion and prevention program that the Pan American Health Organization and World Health Organization created and was adopted to the Honduran context to bring preventative health and nutrition services to children in remote rural areas in Honduras, in the Department of Intibucá. A non-profit organization has been partnering with the government for the past decade to help deliver health into these remote areas in Honduras.

This NGO has developed a program that seeks to improve the nutritional status of young children, and will provide egg vouchers to women who mother children ages 6 to 24 months in January of 2021.

A total of 402 mothers of children will be invited to participate in the survey. An estimated half of which will be from the communities that are covered by the egg intervention and half of children that will be receiving the usual standard of care that live in other communities that will not be covered by the egg intervention.

The communities that received eggs will be matched with similar size and sociodemographic communities from neighboring municipalities to be used as “controls”.

During the government-NGO usual community-health visit, the field workers will explain the purpose of the study. They will also read the informed consent outloud, in addition to providing everyone a physical copy of the consent. In addition, during confirmation of enrollment, the mother will have the opportunity to read the consent again, and voice any questions they may have on their participation. If the mother agrees to participate, then they will proceed to sign the informed consent and medical records -PHI release forms. After these consents have been signed, then the field researchers will proceed to complete the survey. The same survey will also be completed at 6 months and at 12 months. Adherence surveys will be implemented in the communities that are receiving the egg program bimonthly.

1. **Study Procedures**

Both the intervention and control groups will receive the scheduled, standard attention provided during the community-health sessions by the Honduras health services, plus any additional activities planned by the NGO. Even if they don’t want to participate.

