We will review participant’s data entry upon completion of baseline, midline and endline assessments.

1. **Study Withdrawal/Discontinuation**

The participant can manifest their desire to withdraw from the study at any time. They will just have to notify [name], the field coordinator that they no longer wish to participate and she will immediately notify the principal investigator and remove them from the study. The participant will be able to continue receiving any activities that will be receiving without any changes to that.

1. **Statistical Considerations**

To evaluate the intervention effectiveness on growth outcomes, we will use linear mixed models for continuous variables (after transforming if variables do not exhibit a normal distribution) and generalized linear mixed models with logit link for binary outcomes. Full preanalysis plan is published here: <https://osf.io/3gx4e>.

Participant data will be analyzed following an intention-to-treat principle and all available participant data for the particular outcome at baseline,6 and 12 months will be included in analysis. Models will include fixed effects for group, time, and the group x time interaction; whereas, random effects will be used for each child (for correlation of repeated measures over time) and community (for correlation of children within community), to avoid an inflation of type I error rates in the results. All models will be adjusted by age, sex, and baseline growth outcomes. ​

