The field researchers will collect the medical records from the health centers database of only the children who agreed to participate in this study. They will remove any personal identifiers from this medical record database, and include the unique number assigned to the child. This de-identified database will also be uploaded in an IU secured drive to be shared with the PI.

Once these photos have been digitalized, they will be eliminated immediately. The database with identifiers will be stored in an IU secured drive. All data will be scrutinized for plausibility and data entry errors.

1. **Privacy/Confidentiality Issues**

To protect the participant’s privacy and confidentiality, the field staff will collect data in a private space. The surveys collected will not have names, home addresses or phone numbers. Only a code that can only be linked by the field researchers if needed. The data shared with the US investigators of the 402 children will have the child’s sex, date of birth, and municipality (after unblinding). The US team will not have any direct contact with any participant, and the field staff will only contact the participants during the monthly community-health activities where is expected to connect with the researchers, unless participants actively reach out to the field staff.

We cannot guarantee absolute confidentiality. The participants personal information may be disclosed if required by law. No information which could identify the participants will be shared in publications about this study.

Organizations that may inspect and/or copy your research records for quality assurance and data analysis include groups such as the study investigator and his/her research associates, and collaborators, the Indiana University Institutional Review Board or its designees, the Indiana Center for Translational Research (CTSI), and any state or federal agencies who may need to access your medical and/or research records (as allowed by law).

1. **Follow-up and Record Retention**

Deidentified records will be maintained indefinitely. Identifiers except for child’s sex will be erased about 24 months after the data collection aspect and publications of the study have been completed.

1. **References**

1. Iannotti, L.L., et al., *Eggs early in complementary feeding increase choline pathway biomarkers and DHA: a randomized controlled trial in Ecuador.* Am J Clin Nutr, 2017. **106**(6): p. 1482-1489.

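### As written, the age covariate does not adjust the change in LAZ (group x time) for age, although children enter at 6 to 24 months and groups are not randomised

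*Protocol*

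**What the plan says.** All references are to the protocol.

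- **Statistical Considerations, data:** "all available participant data for the particular outcome at baseline,6 and 12 months will be included in analysis". Baseline is listed among the analysed time points.
- **Statistical Considerations, model:** "Models will include fixed effects for group, time, and the group x time interaction", and "random effects will be used for each child (for correlation of repeated measures over time) and community". No other interaction is named.
- **Statistical Considerations, covariates:** "All models will be adjusted by age, sex, and baseline growth outcomes". Whether age means age at entry or age at the visit is not said. The section points to a published pre-analysis plan for full detail; that plan is not at hand.
- **Statistical Considerations, power:** the calculation is for change from baseline at 12 months.
- **Outcome Measures:** the primary outcome is worded as higher LAZ in the egg group at 6 and at 12 months, which is a comparison of levels.
- **Eligibility Criteria:** "Healthy children ages 6 to 24 months at the time the study begins".
- **Enrollment:** "The communities that received eggs will be matched with similar size and sociodemographic communities from neighboring municipalities". Child age is not among the matching factors named.
- **Privacy/Confidentiality Issues:** date of birth is among the data the investigators will receive.

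**The concern.** Children who enter at 6 months and at 24 months are at different stages of early growth, so their expected change in LAZ over the next year may differ. The egg and control communities were not formed by randomisation, and nothing stated makes their age mix equal. If the age mix differs and change depends on entry age, the difference passes into the estimated egg effect.

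The sponsor evidently means to guard against this, since age is in the covariate list. A reader of that list would take the estimated change to be age-adjusted. With the terms as listed, it is not.

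**Working it through.** **1. The plan's own figures.** Detectable d = (1.960 + 0.842) x sqrt(2/n).

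- n = 140 per group: 0.335 (0.336 by the t-test), against 0.34 in the protocol.
- Effective n = 80 per group: 0.443 (0.446 by the t-test), against 0.45 in the protocol.

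Both reproduce. Neither depends on the age adjustment, so this point changes no stated sample-size figure.

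**2. Why the age term cancels.** Write the linear model for child i at visit t as

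Y(i,t) = m + g·G(i) + τ(t) + γ(t)·G(i) + β·x(i,t) + child + community + error,

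with τ and γ zero at baseline, and take the 12-month value minus the baseline value.

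- x = age at entry a(i): β·a(i) − β·a(i) = 0.
- x = linear age at visit, with visits at nominal times: β·(a(i) + 12) − β·a(i) = 12β. This is the same for every child and is absorbed in the visit effect.
- x = baseline LAZ entered as a main effect: it cancels in the same way.
- The child and community intercepts cancel too.

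What remains is τ(12) + γ(12)·G(i) + error, with no age in it. A term δ(12)·a(i), which is age at entry x visit, does not cancel. If it is needed but left out, the bias in γ(12) is δ(12) x (mean entry age in egg group − mean entry age in control group).

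**3. Check by fitting.** One simulated data set was fitted with complete data and one with about 30% dropout. Assumptions: 26 communities of 15 children, true egg effect 0, change rising by 0.03 LAZ per month of entry age, egg children older by 2.2 months (complete data) or 2.6 months (dropout). The 12-month group x time estimates were:

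| Terms added to group, time, group x time | Complete data | About 30% dropout |
|---|---|---|
| none | 0.11791 | 0.09452 |
| entry age, sex | 0.11791 | 0.09453 |
| linear age at visit, sex | 0.11791 | 0.09453 |
| entry age, sex, baseline LAZ | 0.11791 | 0.08672 |
| entry age x visit, sex | 0.05089 | 0.02773 |

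With complete data the shift from adding age x visit is 0.11791 − 0.05089 = 0.067, against 2.2 x 0.03 = 0.066 from the formula in step 2. The remaining 0.051 is sampling error (SE 0.051). These fits show the cancellation and the shift; they do not estimate the bias in this trial.

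**4. Possible size, on assumptions.** The documents give no slope of LAZ on age, no SD of change and no age imbalance. Assume LAZ falls linearly by L between 6 and 24 months and is flat afterwards, with entry ages roughly uniform on 6 to 24 months.

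- Expected 12-month change for entry age a is −(L/18) x min(12, 24 − a).
- Its covariance with a is (L/18) x 20 = 1.11L, and the variance of a is 18²/12 = 27.
- The slope is therefore 1.11L/27 = 0.041L per month of entry age.

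Absolute bias in LAZ (downward if the egg children are the younger group):

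| L | 1 month | 2 months | 3 months |
|---|---|---|---|
| 0.4 | 0.016 | 0.033 | 0.049 |
| 0.8 | 0.033 | 0.066 | 0.099 |
| 1.2 | 0.049 | 0.099 | 0.148 |

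A separate simulation over the same grid gave 0.01 to 0.125. The overall range is roughly 0.01 to 0.15.

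For scale, with an assumed SD of change of 0.65, the planned d = 0.45 is 0.45 x 0.65 = 0.29 LAZ. At L = 0.8 the bias is then 11%, 23% or 34% of that target for 1, 2 or 3 months.

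**5. Other readings of the plan.**

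- Only the 6- and 12-month values as responses, baseline LAZ as covariate (complete-data set of step 3): the 12-month group difference is 0.082 without age and sex and 0.051 with them. Here the age term does adjust.
- With L = 0.8 and egg children 2 months younger, unadjusted change is biased by about −0.067. With 6- and 12-month responses, baseline LAZ and an age main effect, the bias is about −0.022. With the 12-month response alone it is about 0.
- For the 12-month level difference from the three-visit model with age as a main effect, it is about −0.037.

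**The case against.** The strongest reply is that the protocol never says age enters as a main effect only. It lists covariates and refers to a fuller pre-analysis plan, and the form of a covariate is commonly left to such a plan. A reader might infer that the protocol rules out age x visit; it does not, and the linked plan may contain it. What stands is that group x time is the one interaction named, and the covariates as listed do not achieve their evident purpose for the change contrast.

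Second, adjusting for the baseline outcome suggests a model of follow-up LAZ given baseline, in which an age main effect works. This stands as a possible intention. It is not the literal reading, because baseline is listed among the analysed time points.

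Third, the primary outcome is worded as a level difference. A reader might infer that age drops out of every analysis. It does not: it stays partly effective for the 12-month level, and the exact cancellation does not carry over to the logit models.

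Fourth, the sizes are assumed. Both groups share the same entry window. With uniform ages, chance alone gives the difference in mean age an SE of 5.2 x sqrt(2/200) = 0.52 month with 200 independent children per group, so a gap of 2 to 3 months would need a systematic difference between communities. A reader might infer a known bias or a known inflation of type I error. The documents support neither, and chance imbalance is already part of the standard error.

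**Conclusion.** The point holds for the linear models as the Statistical Considerations section reads, with all three visits as responses and no age x time term. The group x time estimate of change, which is the quantity powered, is then not adjusted for age. This is exact with complete data and nearly so with dropout. It holds for entry age and for linear age at visit; a curved function of age at visit would bring in an age x time product and so adjust in part.

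Whether it biases this trial is unknown. Bias needs both a difference in age mix and a dependence of LAZ change on entry age. Under the assumptions in the working it runs from roughly 0.01 to 0.15 LAZ and is small at 1 month's imbalance. It is smaller or absent if baseline LAZ is only a covariate, and smaller if the 12-month level is the contrast tested. The case for acting is that the design is not randomised, the entry window is wide, child age is not a stated matching factor, and the remedy is close to free.

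**What to change.** In Statistical Considerations and in the pre-analysis plan, if it does not already do so:

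- Define age as age at baseline, computed from date of birth.
- Add age at baseline x visit alongside group x visit in the LAZ, WAZ and WHZ models. Linear age or a prespecified flexible form will do; nothing in the documents calls for a particular knot.
- Alternatively, to the same end, model the 6- and 12-month outcomes with baseline outcome and age at baseline as covariates, each allowed to differ by visit. This also settles whether baseline is a response or a covariate.

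The cost is a sentence or two and a few degrees of freedom (two for linear age across two follow-up visits). No new data are needed, since date of birth is already to be supplied.

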With 200 children enrolled in the intervention (egg) group and 200 in the controls, we expect 140 per group to complete all 12 months. We would then have 80% power to detect a significant difference (two-sided alpha=0.05) in outcomes at 12 months (changes from baseline) between groups if the true effect size is at least 0.34 (“med/small”) for Cohen’s d (M1-M2/SD), in a simple comparison (t-test) of means if all observations are independent. In actual analysis, all 402 children will be included in linear mixed models where partial data will be included for those who dropout which will provide higher power than the completers-only analysis. Because children’s data are clustered within community in the mixed models, power is influenced by the correlation of children’s outcomes within communities. In cluster sampling, the power/sample sizes are influenced by the design effect (DE) and interclass correlation (ICC) from correlation within cluster (DE = 1 + (m-1) x ICC, where m is sample size within cluster.) With an average of approximately 15 children per community (m), and a conservative ICC of 0.1, the DE=1+15*.1=2.5. The true sample size of 200 per group may then only be as effective as a sample size of 80 (=200/2.5), and effect sizes will need to be “medium” d=0.45 to maintain 80% power with 0.05 type I error rate, with this clustered design.

**For qualitative information**, direct content analysis to organize and examine the data will be completed by two different researchers. Categories will be identified and coded to determine consistency, frequency, and context until saturation. Information will be then synthesized and analyzed.

1. **Statistical Data Management**

The field researchers will collect data in paper surveys. The paper surveys will not be identified with the name of the participant but with a code that will be linked to a list with the names and codes of the participants and will be stored in a locked cabinet. The paper surveys will also be stored in a lock cabinet in a secured office in the headquarters of Shoulder to Shoulder/Hombro a Hombro until the study finalizes. The field staff will transcribe those surveys to an excel spreadsheet. In the case that they are falling behind, they will take photos of the survey answers. The photos will be uploaded to an IU secured shared drive in either google drive or Microsoft teams so that the IU-investigator can help digitalizing the answers into the excel spreadsheet.

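### The clustered power statement (80% at d=0.45) counts all 200 enrolled children per group and so drops the plan's own 30% loss; on the expected 140 completers power is about 76%

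*Protocol*

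**What the plan says.** All of this stands in one paragraph of the Protocol's Statistical Considerations.

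- **Enrolment and loss.** The paragraph starts "With 200 children enrolled in the intervention (egg) group and 200 in the controls" and continues "we expect 140 per group to complete all 12 months", a loss of 60 out of 200, or 30%.
- **Unclustered figure.** On those 140 it claims "80% power to detect a significant difference (two-sided alpha=0.05) in outcomes at 12 months (changes from baseline) between groups". The claim is made for a Cohen's d of 0.34 or more and is limited to the case "in a simple comparison (t-test) of means if all observations are independent".
- **Bridge.** It then says that the mixed models will use all 402 children, with partial data from dropouts, and that this gives more power than analysing completers only. No size is given for that gain.
- **Clustered figure.** The design effect is defined as 1 + (m-1) x ICC. With about 15 children per community the paragraph evaluates it as follows: "and a conservative ICC of 0.1, the DE=1+15*.1=2.5". It concludes: "The true sample size of 200 per group may then only be as effective as a sample size of 80 (=200/2.5"), so that d=0.45 is needed to keep 80% power.

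**The concern.** The two power figures use different sample sizes, and the change from 140 to 200 happens just where the clustering correction comes in. A reader will take the second figure as the first one adjusted for clustering. In fact it is adjusted for clustering with the attrition adjustment removed. Dividing 200 by the design effect is right only if all 200 children per group supply a 12-month value, or if the mixed model recovers the equivalent information from those who do not. The paragraph itself expects 60 per group not to complete.

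The clustered figure is the protocol's final statement of how sensitive the study is on its growth outcomes, including the primary one, length-for-age z-score. If the result is null, d=0.45 is the effect that readers will think the study had 80% power to find.

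**Working it through.** **Inputs (Protocol, Statistical Considerations).** 200 enrolled and 140 completers per group; two-sided alpha 0.05; ICC 0.1; m about 15 children per community; DE = 1 + (m-1) x ICC. Effective n per group = N/DE. Power comes from the two-sample t-test (noncentral t with noncentrality d x sqrt(n/2) and 2n-2 degrees of freedom).

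**Step 1: reproduce the plan's figures.**
- Independent case, n=140: power at d=0.34 is 80.9%; detectable d at 80% power is 0.336. Agrees with 0.34.
- Clustered case, n=200/2.5=80: power at d=0.45 is 80.8%; detectable d is 0.446. Agrees with 0.45.

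So the printed conclusion follows from an effective n of 80. What needs checking is where the 80 comes from.

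**Step 2: correct the design effect only.** With m=15 the printed formula gives 1 + 14 x 0.1 = 2.4, and 200/2.4 = 83.3. Power at d=0.45 rises to 82.3% and detectable d falls to 0.437. The slip works against the study, not for it.

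**Step 3: put the expected completers in.** The plan's inputs imply 200/15 = 13.3 communities per group. If children drop out individually and the communities remain:
- m at 12 months = 140/13.3 = 10.5
- DE = 1 + 9.5 x 0.1 = 1.95
- effective n = 140/1.95 = 71.8
- power at d=0.45 = 76.4%; detectable d = 0.471

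**Step 4: sensitivity to degrees of freedom.** With about 13 communities per group, 2 x 13 - 2 = 24 cluster degrees of freedom. The Step 3 case then gives 73.5% power and detectable d=0.487. The community count is inferred, so this is a check and not the main result.

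**Step 5: how much must partial data recover?** With 13.3 communities per group and ICC 0.1, 80% power at d=0.45 needs about 172 full 12-month observations per group (m=12.9, DE=2.19, effective n=78.5). That is 32 more than 140, so the model would have to recover about half of the information lost with the 60 dropouts (32/60 = 53%).

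To see whether that is plausible, assume monotone dropout, with p of the 60 dropouts having a 6-month value. Let R² be the share of within-community 12-month variance that the 6-month value predicts. Neither p nor R² is given in the protocol. Per group, with unit variance:

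1/effective n = 0.1/13.3 + 0.9 x [(1-R²)/140 + R²/(140+p)]

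| R² | p=30 (half) | p=60 (all) |
|---|---|---|
| 0.25 | 77.2% | 77.8% |
| 0.50 | 78.1% | 79.3% |
| 0.64 | 78.6% | 80.1% |
| 0.80 | 79.1% | 81.1% |

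With p=0 the formula returns the 71.8 of Step 3. Power reaches 80% only when essentially every dropout attends the 6-month visit and that visit is strongly predictive (R² near 0.64, a correlation near 0.8).

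**The case against.** The strongest reply is that 76% is a completers-only figure, while the planned analysis is not. The protocol specifies a mixed model on baseline, 6-month and 12-month data and says that dropouts' partial data enter it. That stands in part: under the assumptions of Step 5 it brings power to between 77% and 81%, so the likely shortfall is a few points. It does not support dividing 200 by the design effect, which amounts to full recovery, and a child seen only at baseline adds nothing to the estimate of change.

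A second reply is that the protocol calls its ICC conservative. With 140 completers, m=10.5 and ICC 0.08, DE is 1.76, effective n is 79.5 and power is 80.5%; at ICC 0.05 it is 87%. Adjustment for baseline, age and sex may also add precision. This is fair, and it is why the right wording is that 80% is not shown, not that it is false. Still, the protocol makes its claim at ICC 0.1, and at that value the claim needs the 200.

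Three stronger readings are tempting and not supported.
- **That the design-effect slip costs power.** Step 2 shows the opposite.
- **That power is only about 67% (detectable d=0.52).** This comes from 140/2.4 = 58.3, which keeps 15 children per community and so leaves 140/15 = 9.3 communities per group. Whole communities would have to be lost, whereas the paragraph describes children dropping out.
- **That confusing invited with enrolled undermines the calculation.** The Enrollment section does say "A total of 402 mothers of children will be invited to participate in the survey", and the sample-size paragraph treats about that number as enrolled. But the calculation starts from 200 enrolled per group and uses no invitation or refusal rate, so this is a matter of labelling.

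**Conclusion.** The point holds in a limited form. The clustered statement leaves out the plan's own 30% loss, so 80% power at d=0.45 is not shown. On 140 completers per group, with ICC 0.1 and about 13 communities per group retained, power at d=0.45 is about 76% and the detectable effect is about d=0.47; with about 24 cluster degrees of freedom these become about 73% and d=0.49. Credit for partial data narrows the gap by a few points and closes it only under favourable assumptions that the protocol does not state. The result rests on loss spread evenly over communities and on a community count inferred from 200/15. The design-effect error is real but minor and conservative. No endpoint, model or sample size is affected; what is wrong is the stated sensitivity of the design.

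**What to change.** In Statistical Considerations, base the clustered figure on expected 12-month completers: effective n = 140/DE, with DE = 1 + (m-1) x 0.1 and m the number of children per community at 12 months. With the present inputs this gives a detectable effect of about d=0.47, or equivalently about 76% power at d=0.45.

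Alternatively, keep a figure that credits dropouts, but state how many are expected to have a 6-month value and the assumed correlation between visits, and show the resulting effective sample size.

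In either case, correct the design effect for m=15 from 2.5 to 2.4 wherever it is still quoted.

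The cost is a revised paragraph and a slightly less favourable detectable effect. No extra children are needed.
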